
#### Secondary exploratory outcomes

2.4.6

•Changes in comorbid depressive symptoms: To capture a hypothesized decline in comorbid depressive symptoms, we will employ the *Patient Health Questionnaire-9* (PHQ-9; Kroenke et al., 2001). The PHQ-9 is a validated depression measure that assesses the severity of depressive symptoms on nine items using a 4-point Likert scale and has an internal consistency of Cronbach's α = .86 (Kroenke et al., 2001).•Changes in comorbid anxiety symptoms: Changes in comorbid anxiety symptoms will be measured with the *General Anxiety Disorder Scale**-7* (GAD-7; Löwe et al., 2008). The GAD-7 contains seven items answered on a 4-point scale and reliably measures generalized anxiety disorder symptoms (Cronbach's α = .89).•Changes in self-esteem: Possible improvements in self-esteem will be assessed as a core treatment target of eating disorders (Linardon et al., 2019). To address this goal, the *Rosenberg Self-Esteem Scale* will be used (RSES; Roth et al., 2008), consisting of 10 items answered on a 4-point scale with an internal consistency of Cronbach's α = .88 (Roth et al., 2008).•Changes in emotion regulation difficulties: Assumed decreases in emotion regulation difficulties following the intervention will be assessed using the *Difficulties in Emotion Regulation Scale* (DERS; Gratz and Roemer, 2004). The DERS consists of 36 items answered on a 5-point scale, and Cronbach's α ranges between .80 and .89 for the subscales and .93 for the total score.•Use of emotion regulation strategies: The *Heidelberg Form for Emotion Regulation Strategies* (HFERST; Izadpanah et al., 2019) will be employed to assess the use of eight emotion regulation strategies (i.e., rumination, reappraisal, acceptance, problem solving, suppression of emotional expression, suppression of emotional experience, avoidance, social support) that have been associated with eating psychopathology (Prefit et al., 2019). The HFERST consists of 28 items answered on a 5-point scale, and Cronbach's α for the subscales ranges between α = .78 and α = .86 (Izadpanah et al., 2019).•Ecological momentary assessment (EMA): An EMA protocol will be implemented on participants' mobile devices for five days at baseline and post-treatment using signal-contingent measurements at five random times each day and additional event-contingent assessments after episodes of binge eating (Munsch et al., 2007; Munsch et al., 2019; Schaefer et al., 2020). At every assessment, we will employ validated EMA items to measure affect (Watson and Clark, 1994), emotion regulation strategies (Izadpanah et al., 2019; Pruessner et al., 2021), and regulatory difficulties in daily life (Lavender et al., 2017). Binge eating episodes will be assessed based on the DSM-5 criteria for BED (APA, 2013; Munsch et al., 2009; Schaefer et al., 2020). Moreover, we will capture compensatory behavior, body image perceptions (Hilbert et al., 2007), and eating disorder urges using scales employed in previous intensive longitudinal designs (Tasca et al., 2009).

#### Other measures

2.4.7

•Attitudes towards online interventions: Two subscales of the *Attitudes Towards Psychological Online Interventions Scale* (APOI; Schröder et al., 2015) will be used to assess attitudes towards web-based interventions. The selected subscales consist of eight items rated on a 5-point scale and reliably measure perceived technologization threat (α = .64) and anonymity benefits of online interventions (α = .62; Schröder et al., 2015).•Patient outcome expectancies: Treatment motivation will be investigated using the *Patients' Therapy Expectation and Evaluation Scale* (PATHEV; Schulte, 2008). The PATHEV consists of 16 items answered on a 5-point scale and has been shown to reliably assess treatment motivation (α > .73; Schulte, 2005).•Negative intervention effects: The *Negative Effects Questionnaire* (NEQ; Rozental et al., 2019) will be utilized to capture possible side effects of the intervention. For each of the 32 items, participants answer whether an adverse effect occurred (yes/no), how it was (0 to 4) and if they attribute the negative effect to the web-based intervention or something else. The NEQ has an excellent internal consistency of Cronbach's α = .95 (NEQ; Rozental et al., 2019).•Use of other healthcare services: The *Client Sociodemographic Service Receipt Inventory – European Version* (CSSRI-EU; original: Chisholm et al., 2000; Roick et al., 2001) will be employed to assess the use of various other healthcare services (e.g., psychotherapy sessions, contact with psychiatrists). The CSSRI-EU has been validated as a reliable measure in clinical and non-clinical populations (Chisholm et al., 2000; Roick et al., 2001).•Patient adherence: The log files on the online platform (*Selfapy*) will be utilized to capture patient adherence within the intervention group. This includes the times and dates participants log into the intervention and the number of completed modules. Moreover, after six and twelve weeks (mid- and post-treatment assessment), participants in the intervention group will be asked to report how frequently they accessed the web-based intervention.

### Statistical methods

2.5

The analysis strategy for this trial consists of four steps: (1) descriptive analyses, (2) confirmatory analyses of the primary outcome, including sensitivity analyses, (3) analyses of secondary outcomes, including sensitivity analyses, (4) moderator and mediator analyses as well as analyses of the naturalistic EMA measures. All statistical tests will be conducted using R Statistics (R Core Team, 2020); see the R script in the supplementary materials (Supplement S2).

#### Primary and secondary outcome analyses

2.5.1

To statistically evaluate the effectiveness of the web-based intervention for patients with BED compared to the waitlist control condition, growth models within a multilevel modeling (MLM) framework will be conducted. MLMs are regression-based models that allow considering the nested data structure, i.e., the three repeated assessments (level 1) nested within patients (level 2), define change as a continuous process, and have more power when handling missing data than traditional approaches (Hesser, 2015; Kahn and Schneider, 2013; Tasca and Gallop, 2009). To test whether there is a treatment × time interaction effect, we will set up MLMs of increasing complexity (Kahn and Schneider, 2013). The first model will have only random intercepts on the person-level (level 1), and no predictors will be included. In the second model, the fixed effects of time (study entrance, 6 weeks, 12 weeks) and treatment (intervention versus control group) will be added. In a final model, we will examine if the change in symptom severity differs between the intervention and control group by adding the treatment × time interaction. Model fit of the competing models will be compared employing likelihood ratio tests for nested models and the Akaike Information Criterion. A significant treatment × time-interaction with a more substantial change in participants undergoing the 12 weeks of treatment compared to the waitlist group will indicate confirmation of the hypotheses (Raudenbush and Bryk, 2002). The magnitude of treatment effects will be estimated as Cohen's *d* effect size (Feingold, 2013).

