#### Outcomes

2.4.3

Primary and secondary outcome measures will be assessed at baseline (study entrance), six weeks after baseline (mid-treatment), and 12 weeks after baseline (post-treatment). Moreover, to continuously evaluate core eating disorder symptoms, the occurrence of binge eating episodes and overeating will be monitored weekly, and traditional self-reports will be complemented by EMA using mobile technology to capture treatment outcomes and mechanisms in the natural environment and increase the ecological validity of our data. All measures will be collected using the computer software *SoSci Survey* (Leiner, 2021) and made available to participants at http://www.s2survey.net/. An overview of the clinical outcome measures based on the SPIRIT recommendations (Chan et al., 2013) is provided in Table 2.

**Table 2 t0010:** SPIRIT schedule of the randomized controlled trial.

	Study period				
	Enrollment	Allocation	Post-allocation		Close-out
		*Study entrance*	*Weekly*	*Mid-treatment*	*Post-treatment*
Timepoint	*−t*_*1*_	*t*_*1*_	*week*_*1*_*–week*_*12*_	*t*_*2*_	*t*_*3*_
Enrollment					
Eligibility screen	+				
Informed consent	+				
*Clinical interviews*					
Eating Disorder Examination Interview (EDE)	+				
Diagnostic Interview for Mental Disorders (DIPS-OA)	+				
*Allocation*		+			
Intervention					
12-week web-based intervention *Selfapy* for binge eating disorder			+	+	
12-week waiting time			+	+	
Assessments					
*Primary outcome*					
Number of Binge Eating Episodes (EDE-Q)		+		+	+
*Secondary confirmatory outcomes*					
Eating Disorder Examination Questionnaire (EDE-Q)		+		+	+
Weekly Binges Questionnaire(WBQ)		+	+	+	+
Clinical Impairment Assessment (CIA)		+		+	+
World Health Organization Well-Being Index (WHO-5)		+		+	+
*i*MTA Productivity Cost Questionnaire (*i*PCQ)		+		+	+
*Secondary exploratory outcomes*					
Patient Health Questionnaire Depression Scale (PHQ-9)		+		+	+
Generalized Anxiety Disorder Scale (GAD-7)		+		+	+
Rosenberg Self-Esteem Scale (RSES)		+		+	+
Difficulties in Emotion Regulation Scale (DERS)		+		+	+
Heidelberg Form for Emotion Regulation Strategies (HFERST)		+		+	+
Ecological Momentary Assessment (EMA)		+			+
*Other measures*					
Client Sociodemographic Service Receipt Inventory (CSSRI)		+		+	+
Negative Effects Questionnaire (NEQ)				+	+
Attitudes Towards Online Interventions (APOI)		+			+
Patients' Therapy Expectation and Evaluation Scale (PATHEV)		+		+	+

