#### Secondary confirmatory outcomes

2.4.5

•Changes in global eating psychopathology: Global eating psychopathology will be investigated as a secondary outcome using the total score of the EDE-Q (Hilbert et al., 2007), which is derived from the dimensions of *weight concern*, *shape concern*, *eating concern*, and *restraint*. The eating psychopathology dimensions are assessed with 22 items on a 7-point Likert scale and Cronbach's α ranges between .85 and .93 for the subscales and .97 for the total score (Hilbert et al., 2007).•Changes in the weekly frequency of binge eating episodes, overeating, and regular eating: The *Weekly Binges Questionnaire* (WBQ; Munsch et al., 2007; Munsch et al., 2019) will be used as a continuous method to monitor the frequency of objective and subjective binge eating episodes and overeating as secondary outcomes of BED symptom alterations. Weekly text messages throughout the study period will remind participants to report the occurrence and rate the severity of each of these eating episodes as well as regular eating within the last week on an 11-point scale (Munsch et al., 2007; Munsch et al., 2019).•Changes in eating-disorder-related clinical impairments: To assess hypothesized reductions in clinical impairments specific to eating disorders, we will employ the *Clinical Impairment Assessment* scale (CIA; Bohn et al., 2008), which measures overall and domain-specific impairments (i.e., cognitive, social, and personal). The CIA consists of 16 items rated on a 7-point Likert scale and demonstrates excellent internal consistency (Cronbach's α = .97), construct validity, and sensitivity to change (Bohn et al., 2008).•Changes in well-being: To measure assumed increases in well-being, we will use the frequently employed *World Health Organization-Five Well-Being Index* (WHO-5; Bech et al., 2003). The WHO-5 assesses general well-being based on five items, rated on a 6-point scale, and has high internal consistency (Cronbach's α = .92; Brähler et al., 2007).•Changes in work capacity: To address the increasing significance of health economic evaluations (Jenkins et al., 2021; Safi et al., 2022), changes in work capacity and productivity will be measured based on the *iMTA Productivity Cost Questionnaire* (iPCQ; Bouwmans et al., 2015). The iPCQ examines absences from work and productivity losses due to sickness-related restrictions in work efficiency. Test-retest reliability of the iPCQ is excellent concerning the reported number of sick leave days (ICC = .83) and moderate regarding the number of days at work while impeded (ICC = .56) and efficiency rates (ICC = .73; Bouwmans et al., 2013).

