#### Additional analyses

2.5.3

Additional statistical tests will be run to aid in interpreting the results and obtain a more nuanced understanding of the findings. Independent *t*-tests and χ^2^-tests will be used to estimate possible between-group pre-treatment differences regarding healthcare service utilization, demographic variables, and eating disorder symptom severity. In case of significant group differences, these variables will be utilized as moderators of the treatment × time interaction effects to test the robustness of the findings. We will further test whether other covariates such as patient outcome expectancies, attitudes towards online interventions, or patient adherence affect changes in the primary outcome. To obtain a higher ecological validity and temporal resolution when examining reductions in core eating disorder symptoms, we will analyze the EMA data and the weekly assessments of binge eating episodes. As patient safety indicators, the percentage of participants in the intervention group who experienced adverse intervention effects caused by the web-based intervention will be quantified, and the amount of impairment due to these negative effects will be calculated. Moreover, we will test potential improvements in emotion regulation difficulties and strategy use as possible mediators of BED symptom change.

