### Strengths and limitations of the study

3.1

We highlight five major strengths of this trial. First, the two-armed randomized controlled design provides a high degree of internal validity, allowing to attribute observed group differences to the web-based intervention with sufficient certainty. Second, the 12-week waiting period for the intervention was chosen to maximize our findings' generalizability and external validity. As such, a waiting time of three months closely reflects care reality for patients with BED in Germany, as awaiting outpatient psychotherapy requires, on average, three to six months (BPtK, 2018). Third, investigations of improvements in well-being and quality of life following web-based interventions remain scarce. To address this gap, we will assess crucial secondary outcome parameters such as changes in self-esteem and work capacity to evaluate whether web-based interventions can improve BED patients' overall daily life experiences apart from symptom reduction. Fourth, according to recent methodological recommendations (Hesser, 2015), our statistical analysis will use a linear mixed models framework. This approach has several advantages over traditional analysis methods, as it allows considering the nested data structure and has more power when handling missing data. Finally, to increase the validity of our findings, the structured diagnostic interviews will be conducted by independent researchers who are blind to treatment conditions. Moreover, biases associated with retrospective assessments will be reduced by closely tracking symptom fluctuations over the study period. To achieve this goal, we will combine classic self-report instruments with weekly reports of eating disorder symptoms (Munsch et al., 2007; Munsch et al., 2019) and naturalistic EMA to obtain a high temporal resolution and ecological validity of measures.

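### The Weekly Binges Questionnaire is a confirmatory secondary outcome collected every week, but the only confirmatory model stated uses three time points, and nothing says which analysis decides

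*Protocol article*

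**What the plan says.** All references are to the protocol article.

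- **Status and schedule.** Table 2 (section 2.4.3) lists "Weekly Binges Questionnaire(WBQ" under the row heading "Secondary confirmatory outcomes", with marks at t1, in the weekly column (weeks 1 to 12), at t2 and at t3. Section 2.4.5 says that the instrument "will be used as a continuous method to monitor the frequency of objective and subjective binge eating episodes and overeating as secondary outcomes".
- **Stated model.** Section 2.5.1 covers primary and secondary outcomes together. It describes a growth model for "the three repeated assessments (level 1) nested within patients (level 2", in which "the fixed effects of time (study entrance, 6 weeks, 12 weeks) and treatment (intervention versus control group) will be added". Its decision rule is a significant treatment × time interaction in favour of the intervention. No exception is made for the WBQ.
- **Weekly series.** Section 2.5.3 (Additional analyses), which introduces its tests as help with interpretation, says "we will analyze the EMA data and the weekly assessments of binge eating episodes". It gives no model, time variable or decision rule.
- **Analysis steps.** Section 2.5 lists "2) confirmatory analyses of the primary outcome, including sensitivity analyses, (3) analyses of secondary outcomes, including sensitivity analyses", and refers to an R script in Supplement S2, which is not at hand.

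**The concern.** The sections do not fit together on what the WBQ is for. It is labelled confirmatory and was chosen because it is continuous. Yet the only analysis with a confirmation rule is built on three assessments. The analysis that uses the weekly reports sits with the interpretive tests and shares a sentence with the EMA data, which Table 2 classes as exploratory.

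Three things follow.

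1. There are two candidate WBQ analyses and no rule between them. If the three-point and weekly results disagree, the choice could be made after the data are seen, which a confirmatory label is meant to prevent.
2. The variable is not fixed either. Section 2.4.5 names objective binges, subjective binges, overeating, regular eating and severity ratings, and marks none of them as the one tested.
3. On the plain reading, the confirmatory test leaves out most of the weekly reports. A patient who leaves at week 5 would enter it with the baseline value only, although up to five weekly reports exist. The Strengths and limitations section itself expects relatively high dropout.

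**Working it through.** **1. The plan's own figure.** Inputs from section 2.6: d = 0.50, intraclass correlation 0.40, power 0.80, alpha 0.05 (two-sided assumed, since sidedness is not stated). Allocation is 1:1 (section 2.3.1). Set the total variance to 1 and use a random-intercept growth model with times 0, 0.5 and 1.

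- Residual variance = 1 − 0.40 = 0.60.
- Sum of squared time deviations = 0.25 + 0 + 0.25 = 0.5.
- Variance of one patient's slope = 0.60/0.5 = 1.2, so SD = 1.0954.
- n per arm = 2 × (1.960 + 0.842)² × 1.2/0.50² = 75.4, rounded up to 76. N = 152, power 0.803.

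The stated N = 152 is reproduced, so it is consistent with the three-point model. A two-point change score gives the same N. Nothing below touches this figure.

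**2. Number of measurements.** Baseline plus weeks 1 to 12 is 13 points, if t2 and t3 fall on weeks 6 and 12. Three of 13 is 23%.

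**3. Best case for using all weeks.** With independent residuals and no variation in patients' slopes, the slope variance is σ²/Σ(t − t̄)².

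- Weeks 0, 6, 12: 36 + 0 + 36 = 72.
- Weeks 0 to 12: 2 × (1 + 4 + 9 + 16 + 25 + 36) = 182.
- SE ratio = √(72/182) = 0.63. The variance is 1 − 72/182 = 60% smaller.

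**4. Patients' slopes vary.** Let r be the share of the three-point slope variance that is true variation between patients. More measurements do not reduce that share, so the ratio is √(r + (1 − r) × 72/182):

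| r (assumed) | SE ratio, 13 points against 3 |
|---|---|
| 0.2 | 0.72 |
| 0.3 | 0.76 |
| 0.5 | 0.84 |

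**5. Neighbouring weeks are correlated.** Take AR(1) residuals with correlation ρ between adjacent weeks, so that the correlation at lag k is ρ^k. Keep the random intercept. The slope variance is the slope element of (X′V⁻¹X)⁻¹, computed once for weeks 0, 6, 12 and once for weeks 0 to 12. The documents give no ρ for the WBQ, so the values are assumed. Variances are in units of σ²:

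| ρ (assumed) | 3 points | 13 points | SE ratio | SE ratio with r = 0.5 added |
|---|---|---|---|---|
| 0 | 0.01389 | 0.00549 | 0.63 | 0.84 |
| 0.3 | 0.01389 | 0.00843 | 0.78 | 0.90 |
| 0.5 | 0.01389 | 0.01079 | 0.88 | 0.94 |
| 0.7 | 0.01370 | 0.01278 | 0.97 | 0.98 |

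All of these assume a linear trend and complete weekly reporting. The gain runs from substantial to almost nil, depending on a correlation that the documents do not supply.

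**The case against.** The strongest reply is that sections 2.5.1 and 2.5.3 can be read together. Section 2.5.1 describes a general model for the many questionnaires given at t1, t2 and t3. The WBQ is the one weekly outcome, and section 2.5.3 commits to analysing it weekly. No sentence says that the WBQ test uses only three points. Section 2.5 attaches the word confirmatory to the primary outcome only, and the missing detail may be in the R script.

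Part of this stands. The three-point test is the plain reading of section 2.5.1 rather than an explicit statement about the WBQ, and the script could settle it. But the conflict lies in the article's own text: Table 2 and section 2.4.5 call the measure confirmatory, while its weekly analysis is placed among additional tests. If the sponsor intends the joint reading, one sentence would say so.

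A reader might also infer more than the documents support:

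- **That the weekly data are discarded, or that reports from dropouts are lost to the trial.** Section 2.5.3 says the weekly assessments will be analysed. On the plain reading, the reports are missing from the confirmatory test only.
- **That the trial cannot show whether its 28-day recall result holds on short recall.** Both the weekly and the EMA data are to be analysed. The Strengths and limitations section says "biases associated with retrospective assessments will be reduced by closely tracking symptom fluctuations over the study period", through combining instruments; it does not claim that the 28-day primary endpoint is corrected. Setting summed weeks 9 to 12 beside the EDE-Q count would be an optional extra, not the repair of a defect.
- **That the WBQ test loses most of its precision.** The 0.63 ratio is a best case, and the tables above show how quickly it moves towards 1.

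**Conclusion.** The point holds as an inconsistency worth correcting. A confirmatory secondary outcome has two possible analyses: one with a decision rule but three time points, the other with the weekly data but no model or rule. The variable to be tested is not named.

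The cost in precision is uncertain. The standard error with all weeks is about 0.63 of the three-point value at best, 0.78 to 0.97 with an assumed weekly autocorrelation of 0.3 to 0.7, and up to 0.98 if half of the three-point slope variance is also true variation between patients. Under a correctly specified model, using all weeks is at least as precise, and it brings in the weekly reports of patients who leave between main assessments. The case for the change therefore rests mainly on fixing the test in advance, with precision as a possible further gain.

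The primary outcome analysis and N = 152 are not affected.

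**What to change.** In section 2.5.1, state that the confirmatory WBQ test is the treatment × time effect on one named WBQ variable, for example the weekly number of objective binge episodes. Fit it to all weekly reports with week as the time variable, and model the within-patient correlation with a random slope, autocorrelated residuals, or both. Then remove the WBQ from section 2.5.3, so that only one analysis can decide its hypothesis.

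The cost is wording and a change to the script, since the data are already in the assessment schedule. The downside is a slightly more complex model.

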### Conclusion

3.2

Bridging the gap between current knowledge about effective BED treatments and available interventions in clinical care is critical for advancing healthcare for this condition. The present randomized controlled trial aims to address this gap by testing whether providing low-threshold access to a web-based intervention for BED in routine care may help patients reduce their core symptomatology and improve their emotional and social well-being. Our findings will thus address the scarcity of studies evaluating the effectiveness of web-based interventions for eating disorders in standard healthcare settings (e.g., Vollert et al., 2019). Finally, to better understand which patients particularly benefit from web-based programs, our randomized controlled trial is designed to test individual treatment trajectories and mechanisms of change. Understanding for whom and why these interventions reduce eating disorder symptoms is essential to providing more targeted, ultimately more effective BED treatments. When successfully integrated into clinical practice, delivering the web-based self-help intervention to individuals in need of services may alleviate the high burden of BED for patients, their families, and society.

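### The confirmatory model is described with random intercepts only, so the treatment × time test can exceed its 5% level if patients' rates of change differ or correlation falls with time

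*Protocol article*

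**What the plan says.** Section 2.5.1 of the protocol article sets out growth models for "the three repeated assessments (level 1) nested within patients (level 2"), in three steps of increasing complexity.

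- Model 1: "The first model will have only random intercepts on the person-level (level 1), and no predictors will be included".
- Model 2: "the fixed effects of time (study entrance, 6 weeks, 12 weeks) and treatment (intervention versus control group) will be added".
- Final model: "we will examine if the change in symptom severity differs between the intervention and control group by adding the treatment × time interaction".

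The nested models are compared by likelihood ratio test and the Akaike Information Criterion (AIC). The hypotheses count as confirmed by "A significant treatment × time-interaction with a more substantial change in participants undergoing the 12 weeks of treatment compared to the waitlist group". Nothing is said of a random slope of time, a residual correlation structure or an unstructured covariance. The coding of time is not fixed outright: the section says that multilevel models "define change as a continuous process", which suggests linear time, but it lists the three visits in a way that would also fit a categorical factor. Section 2.5 refers to an R script in Supplement S2, which is not at hand.

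Section 2.6 gives N = 152 from d = 0.50, an intraclass correlation of .40, power .80 and alpha .05. It gives no slope variance. The Conclusion (3.2) says that "our randomized controlled trial is designed to test individual treatment trajectories and mechanisms of change".

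**The concern.** A linear model with a random intercept and independent residuals forces compound symmetry. Apart from their starting level, patients in an arm are taken to change in parallel, and the correlation between baseline and week 12 is taken to equal that between baseline and week 6. The model therefore uses one pooled within-person variance for every contrast over time. When individual slopes differ, or correlation decays, the baseline-to-week-12 contrast varies more than that pooled figure, so the standard error of the interaction is too small.

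That interaction is the test on which the trial is judged, so both its significance level and its confidence interval are at stake. The article gives reason to expect differing trajectories: it plans to study who benefits most, lets patients choose half of the modules, anticipates uneven adherence, and allows other treatment after randomization in both arms.

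**Working it through.** **Inputs.** From the article: three equally spaced visits (0, 6, 12 weeks), 1:1 allocation, d = 0.50, intraclass correlation .40, power .80, alpha .05 (two-sided assumed). Assumed, because the article does not give them: the slope variance, or the rate at which correlation decays. Data are taken as complete, and mean change as linear.

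**1. The plan's own figure.** Set total variance to 1, so residual variance is 1 − .40 = .60. Scale time 0, 0.5, 1, so its sum of squares is 0.5. With no slope variance, a person's 12-week slope has variance .60/0.5 = 1.2. Then n per arm = 2 × 1.2 × (1.960 + 0.842)² / 0.50² = 75.3, rounded up to 76, giving N = 152 with power .803. This matches.

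A pre-post change score with a baseline/week-12 correlation of .40 has variance 2 × (1 − .40) = 1.2 and so gives the same N = 152. The match therefore does not show which variance assumption was used.

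**2. Type I error when slopes vary.** Let s² be the residual variance and t² the slope variance per 6-week step. The normalised linear contrast (−1, 0, 1)/√2 has true variance s² + 2t². The quadratic contrast (1, −2, 1)/√6 has variance s². The random-intercept model pools the two and uses their mean, s² + t². Hence:

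- true/model variance R = (s² + 2t²)/(s² + t²)
- type I error = 2 × [1 − Φ(1.96/√R)]

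| t²/s² (assumed) | R | √R | 1.96/√R | Type I error |
|---|---|---|---|---|
| 0 | 1.000 | 1.000 | 1.960 | 5.0% |
| 0.1 | 1.2/1.1 = 1.091 | 1.044 | 1.877 | 6.1% |
| 0.2 | 1.4/1.2 = 1.167 | 1.080 | 1.815 | 7.0% |
| 0.5 | 2.0/1.5 = 1.333 | 1.155 | 1.697 | 9.0% |

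Simulation with 20,000 trials per setting agrees with the closed form. In it, a test that estimates the slope variance stayed at 4.6% to 5.2%. As t² grows without bound, R tends to 2 and type I error to 16.6%.

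To judge scale with s² = .60: t²/s² = 0.1 means a 12-week slope variance of 4 × .06 = .24, an SD of 0.49, about the size of the assumed effect. The last row means 4 × .30 = 1.20, more than the whole baseline variance, so it is an extreme case.

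**3. Type I error when correlation decays.** With equal variances, the linear contrast has variance 1 − r₁₃ and the quadratic contrast [6 + 2(r₁₃ − 4r₁₂)]/6, where r₁₂ is the correlation 6 weeks apart and r₁₃ that 12 weeks apart.

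| r₁₂, r₁₃ (assumed) | Linear | Quadratic | Mean | R | Type I error |
|---|---|---|---|---|---|
| .4, .4 | .600 | .600 | .600 | 1.000 | 5.0% |
| .5, .4 | .600 | .467 | .533 | 1.125 | 6.5% |
| .6, .4 | .600 | .333 | .467 | 1.286 | 8.4% |

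**4. Categorical time.** A joint two-degree-of-freedom interaction test from the random-intercept model rejected in 4.9% to 5.5% of simulated null trials, for 12-week slope variances from 0 to 1.20. The single arm × week-12 coefficient is different. With balanced data it is the same contrast as the linear slope, and it is inflated to the same degree.

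**5. Power at N = 152 under a correctly specified model.** The answer depends on what the .40 stands for.

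- If it is the baseline/week-12 correlation, the contrast variance is 1.2 and power stays at .80 whatever the week-6 correlation.
- If it is an intraclass correlation at zero slope variance, with slope variance added on top, then t²/s² = 0.1 gives 1.2 + .24 = 1.44 and power .73. A ratio of 0.2 gives 1.2 + .48 = 1.68 and power .66.

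**The case against.** The strongest reply is that the phrase about random intercepts describes only the first, predictor-free model. The article never says outright that the random part stays unchanged, and the formula may be in Supplement S2. That limits what can be said about the analysis that will be run. It does not clear the text, which lists what each later step adds, and each addition is a fixed effect. If the script does contain a random slope, section 2.5.1 misdescribes the confirmatory model and needs the same correction.

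Second, a reader might infer that the false-positive rate is certainly above 5%. The documents do not support that. The excess needs varying slopes or decaying correlation, neither of which is quantified, and a linear-time or single week-12 contrast, which the article suggests but does not fix. If time is categorical, the likelihood ratio test of the final model against the second is the joint test, which stays near 5%. But the article's criterion is directional, a larger change under treatment, and that points to a single contrast. The remark in the Conclusion about individual trajectories makes varying slopes plausible; it does not give their size.

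Third, a reader might infer from the match to N = 152 that the sample size assumes zero slope variance and that the trial is therefore underpowered. This does not follow, because a pre-post change with correlation .40 gives the same N. Section 2.6 also refers to further power analyses in Fig. S3, which is not shown.

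**Conclusion.** The point holds in conditional form. As described, the confirmatory model has a compound-symmetric covariance, and the test that decides the trial is anti-conservative under the kind of heterogeneity the article itself expects. The likely excess is modest: type I error of about 6% to 7% for t²/s² of 0.1 to 0.2, and 6.5% to 8.4% for correlations of (.5, .4) to (.6, .4). Equivalently, the model's standard error is some 4% to 12% too small (1 − 1/√R, from R = 1.091 to 1.286).

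These figures rest on assumed slope variances and correlations, complete data, linear mean change, and a linear or week-12 contrast. There is no excess if slopes do not vary and correlation is constant, and essentially none for a joint two-degree-of-freedom test over the range examined. Although modest, the matter is more than missing detail, because the sequence that is stated leads to the too-small standard error.

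**What to change.** In section 2.5.1 and the R script:

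- State that the confirmatory model has a random intercept and a random slope of time, or an unstructured 3×3 within-person covariance. Fix the choice in advance; do not select it by AIC or likelihood ratio test.
- State whether time is linear or categorical, and which interaction contrast decides the hypotheses.

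In section 2.6, state which variance assumption N = 152 relies on: zero slope variance with an intraclass correlation of .40, or a baseline/week-12 correlation of .40. Reconcile it with the model chosen.

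As a clerical matter, model 1 places the person at level 1, while the same section places patients at level 2. Correct the label; it does not affect the analysis.

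The cost is a few sentences and a line of code. Confidence intervals for the interaction become somewhat wider if slopes do vary.
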